### Randomization, allocation concealment and partly double-blind

2.9

Two groups, each one of 92 independent random numbers, will be generated using Excel 2013 software (Microsoft Corporation, Redmond, Washington) by the third party that does not participate in the study, and will be divided by 4. The remainder will be 1 for group A, 2 for group B, 3 for group C and 0 for group D. A, B, C, D are prescribed as diet + drug, diet + placebo, drug and placebo group, respectively. The number of the drug will be reserved and will be encapsulated and stored in opaque envelopes, preserved by the third party. When a patient is enrolled, an envelope with a sequence number on its surface will be passed to the researchers. The researchers and patients will know whether diet is interfered and the drug number only, but not the corresponding drug or placebo group. When the trial is finished, the third party will uncover the blindness. It is difficult to conduct blinding since the diet intervention is a set of dietary principles, rather than specific food, so only drugs are double-blind to reduce the information bias.

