### Study design

2.2

The protocol was drafted using the SPIRIT guidelines and the results will be reported following the checklist of the Consolidated Standards of Reporting Trials (CONSORT) statement (see Supplementary Table 1). All the participants will be informed about the study purpose and their signed informed consent will be obtained before joining this parallel-group study. A total of 92 participants will be recruited in each TFC or aTFC subtype following the inclusion and exclusion criteria. Then they will be allocated to drug + diet group, placebo + diet group, drug group and placebo group randomly at 1:1:1:1 ratio. The positive drugs are Macrogol 4000 Powder (Forlax, Beaufort Ipsen Industrie) and Chinese herb powder for TFC and aTFC groups respectively. Outcomes will be evaluated at baseline, the 14th day (followed-up by telephone) and 28th day by researchers blinded to the groups. Participants will be informed whether diet intervention is acted by the enrollment number and obtain the “drug” corresponding to the number, but they and the researchers will not know whether they are receiving a drug or a placebo. The whole study design is illustrated (see Fig. 1). A SPIRIT figure for the schedule of enrolment, interventions and assessments is also presented (see Fig. 2).

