### Sample size

2.6

Due to the lack of relevant evidence, this is an exploratory study with small sample size. A total of 92 participants for each subtype will be recruited and will be further divided in four sub-groups (23 participants in every sub-group).

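### The remainder-by-4 rule applied to independent random numbers is simple randomisation, so it does not deliver the fixed 23 per arm stated under Sample size

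*Protocol article*

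**What the plan says.** Three statements in the Protocol article bear on arm size.

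- Section 2.2 (Study design) has participants in each subtype "allocated to drug + diet group, placebo + diet group, drug group and placebo group randomly at 1:1:1:1 ratio".
- Section 2.6 (Sample size) sets the numbers: "A total of 92 participants for each subtype will be recruited", and these "will be further divided in four sub-groups (23 participants in every sub-group").
- Section 2.9 (Randomization, allocation concealment and partly double-blind) gives the mechanism: "Two groups, each one of 92 independent random numbers, will be generated using Excel 2013 software". A third party outside the study does this and divides the numbers by 4. Then: "The remainder will be 1 for group A, 2 for group B, 3 for group C and 0 for group D".

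The article mentions no blocks, ranking, sampling without repeats or other balancing step. The two separate lists stratify by subtype, but they do not balance the four arms within a subtype.

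**The concern.** Section 2.9 spells out the allocation rule, so it can be checked against section 2.6. If the 92 numbers are independent, each patient has a one-in-four chance of each arm whatever happened to the others. Arm counts then vary at random, and nothing pulls them back to 23.

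This matters because section 2.6 rests on no power calculation: "Due to the lack of relevant evidence, this is an exploratory study with small sample size". The arm size of 23 is therefore the main numerical commitment of the design. With arms this small, chance alone can leave one comparison arm noticeably thinner than planned. A person building the list from section 2.9 would not obtain the design described in section 2.6.

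**Working it through.** **Inputs**

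- Patients and random numbers per subtype: 92 (sections 2.6 and 2.9).
- Arms: 4, set by remainder 1, 2, 3 or 0 (section 2.9).
- Stated arm size: 23 (section 2.6).
- Assumption: the numbers are uniform integers, so each remainder has probability 1/4. The article does not give the Excel function or the number range.

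**Step 1. The plan's own figure.** 4 × 23 = 92, so the stated total and arm size agree. The question is whether the rule produces them.

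**Step 2. Distribution under the rule as written.** The four counts follow a Multinomial(92; 1/4, 1/4, 1/4, 1/4) distribution. For one arm:

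- mean = 92 × 0.25 = 23
- SD = √(92 × 0.25 × 0.75) = √17.25 = 4.15
- central 95% binomial range: 15 to 31
- probability that a given arm has exactly 23: 9.6%

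**Step 3. Probability of the stated design.**

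P(23, 23, 23, 23) = 92! / (23!⁴ × 4⁹²) = 0.00114, or about 0.11% in one subtype. For both subtypes it is 0.00114² ≈ 1.3 × 10⁻⁶.

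**Step 4. Typical imbalance (1,000,000 simulated multinomial draws, one subtype).**

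| Quantity | Result |
|---|---|
| Mean smallest arm | 18.2 |
| Mean largest arm | 28.0 |
| P(some arm has 18 or fewer) | 51% |
| P(largest minus smallest is 5 or more) | 91% |
| P(largest minus smallest is 10 or more) | 50% |
| P(all arms between 21 and 25) | 8.3% |

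The last two differences compare the extremes of four arms. For one pair of arms chosen in advance, a difference of 10 or more has probability of about 16%.

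**Step 5. Cost in precision.** For a two-arm comparison the effective size per arm is the harmonic mean, 2n₁n₂/(n₁ + n₂). Over the simulated draws it averages 22.5 for a pair of arms (95% range 17.5 to 27.4), against 23 under exact balance. For an 18 versus 28 split it is 2 × 18 × 28 / 46 = 21.9. As an illustration only, assume a standardised difference of 0.8 and a two-sided 5% t-test; neither is in the article. Power is then 75.6% at 23 versus 23 and 73.6% at 18 versus 28.

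**Step 6. Readings without repeats.**

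| How the 92 numbers are drawn | P(exactly 23 in each arm) |
|---|---|
| Random ordering of 1 to 92, no repeats | 100% |
| No repeats from 1 to 100 | 4.5% |
| No repeats from 1 to 200 | 0.28% |
| No repeats from 1 to 1000 | about 0.13% |

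Of these, only the full permutation of 1 to 92 meets section 2.6, because each remainder then occurs exactly 23 times.

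**The case against.** **The authors may have meant a permutation.** There are exactly 92 numbers per list and 92 = 4 × 23, so a shuffled list of 1 to 92 would fit section 2.6 perfectly. The word *independent* might have been used loosely, for distinct numbers or for separate lists. An article also condenses a fuller document. This is the strongest point, and it limits the conclusion to the rule as written. It does not remove the conflict: the members of a permutation are not independent, the article states the rule step by step, and a reader following it would build a different list. The text would need correcting even if the list is sound.

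**Section 2.2 is not contradicted.** A 1:1:1:1 ratio is compatible with simple randomisation, since each arm has probability 1/4. This stands. The conflict is with the fixed 23 in section 2.6.

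**The consequences are modest.** This also stands. Allocation is unbiased, the trial is declared exploratory with no power claim, and the rank, chi-square and Fisher tests in section 2.15 do not need equal arms.

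**Stronger readings to avoid.** A reader might infer that the randomisation is invalid, or that the comparisons are seriously underpowered; the figures support neither. A reader might also infer that drug supplies will not match the arms, but the article gives no stock plan, and the third party can know the counts before numbering the drugs. Balance over calendar time is uncontrolled under any simple randomisation, and nothing in the article shows that it matters here.

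**Conclusion.** The inconsistency is real and of moderate importance. As written, section 2.9 describes simple randomisation, which gives 1:1:1:1 only in expectation and misses the 23 per arm of section 2.6 in about 99.9% of lists for each subtype. Arms of about 18 and 28 are the typical extremes. The conclusion rests on taking *independent* at face value and on uniform integers.

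The harm is an arm size that the method does not guarantee, with a small average loss of precision (an effective 22.5 per arm against 23). It is not bias, and it does not invalidate any planned comparison.

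**What to change.** Before enrolment, have the same third party generate a restricted list, separately for TFC and aTFC, that guarantees 23 per arm, and amend section 2.9 to match.

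- **Simplest option:** a random permutation of the integers 1 to 92 without repeats, keeping the remainder rule. The only textual change is to replace the reference to independent numbers. Exact balance is reached only once all 92 are enrolled.
- **Alternative:** permuted blocks of varying size, each a multiple of 4 and summing to 92, with block sizes concealed from the researchers. These also hold the arms close to balance during recruitment. The small downside is some predictability: diet allocation is open, and half of every block is assigned to diet.

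If a permutation of 1 to 92 was intended all along, saying so is enough. If a simple-randomisation list is already in use, leave it in place, restate section 2.6 as an expected 23 per arm, and report the actual arm sizes.

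The cost is a new or clarified list from the third party and a sentence or two of text, with no extra staff or patients.

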### Emergency unblinding

2.10

In case of any serious adverse events (SAEs) or emergency, the researcher will report to the supervisor and the main researcher to decide whether to open the emergency letter. Once opened, the case will be treated as exfoliated, excluded from the efficacy analysis, but will remain included in the adverse reaction analysis. Details of the unblinding cause, date, treatment situation and results will be reported in the case report form (CRF) and will be signed by the administrator.

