### AEs

2.13

AEs mean negative effects caused by the treatment. During the study, any abnormal reactions from participants will be reported to the researchers. The occurrence time, side effects, degree, duration and mitigation will be recorded in the CRF.

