### Planned statistical analysis

2.15

Continuous variables will be described as the mean ± standard deviation (SD), median or interquartile range (IQR). The number of cases, frequency, the rate and the constituent ratio will be described by categorical variables. Variance analysis will be used for continuous variables in the baseline data having normal distribution and same variance. Wilcoxon rank sum test or Kruskal–Wallis *H* test will be used for the comparison of differences between groups that are not normally distributed or have uneven variance. Categorical variables will be tested by chi–square test or Fisher exact test. Wilcoxon rank sum test or Kruskal–Wallis *H* test will be used for the number of CSBM per week in primary outcome. Chi–square test or Fisher exact test will be used for percent improvement of each symptom scale score in secondary outcome indicators. The result of 48-h GITT will be analyzed using chi-square or Fisher test. Wilcoxon rank sum test or Kruskal–Wallis *H* test will be used for measurement data in HRAM, while chi-square test or Fisher exact test will be used for counting data. Safety, dietary quality, compliance indicators will be tested by chi-square test or Fisher exact test. Wilcoxon rank sum test or Kruskal–Wallis *H* test will be used to compare the diversity, the relative abundance of bacteria in phylum and genera level between 2 or more groups.^[22]^ Complying with the intent-to-treat (ITT) and per-protocol (PP) principle, all data of the patients randomized and at least 1 assessment (include baseline assessment) will be analyzed. For dropouts and terminations, their missing data will be obtained by last-observation-carried-forward (LOCF) method. All statistical analyses will be performed by SPSS20 software (IBM, Chicago, Illinois), and *P* value <.05 will be considered statistically significant.

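### Section 2.10 drops patients whose emergency letter is opened from the efficacy analysis without limit, in conflict with the intention-to-treat rule in section 2.15

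*Protocol article*

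**What the plan says.** Section 2.10 (Emergency unblinding) sets the trigger for opening the emergency letter: "In case of any serious adverse events (SAEs) or emergency, the researcher will report to the supervisor and the main researcher to decide whether to" do so. The consequence of opening it follows: "the case will be treated as exfoliated, excluded from the efficacy analysis, but will remain included in the adverse reaction analysis". The only analysis named for the exclusion is efficacy as a whole.

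Section 2.15 (Planned statistical analysis) defines who is analysed. It starts from "Complying with the intent-to-treat (ITT) and per-protocol (PP) principle" and continues "all data of the patients randomized and at least 1 assessment (include baseline assessment) will be analyzed". On patients who stop early it adds: "For dropouts and terminations, their missing data will be obtained by last-observation-carried-forward (LOCF) method". It makes no exception for patients whose letter has been opened.

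Three other places bear on the point. Section 2.13 (AEs) states that "AEs mean negative effects caused by the treatment". Section 2.9 says that the researchers know whether a patient is on the diet, but not whether the powder is drug or placebo. Section 2.6 plans 23 patients per arm in each subtype.

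**The concern.** ITT analysis keeps each patient in the randomised arm whatever happens later, so that the arms stay comparable. Section 2.10 removes patients because of something that happens after randomisation. Removal takes two steps, and either may differ by arm:

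- **The event.** The arms differ in active drug or placebo and in diet, so serious events or emergencies may not occur equally often in them.
- **The decision to open.** It is taken case by case, and the researcher who reports the event already knows the diet allocation.

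If either step is related to both arm and outcome, the remaining patients no longer form a randomised comparison. At stake is who enters the primary comparison of complete spontaneous bowel movements (CSBM) per week. With two conflicting rules, that choice could end up being made after allocation and outcome are known for the patient in question.

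**Working it through.** **Step 1. The two rules side by side, for a randomised patient with baseline data whose letter is opened.**

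| Question | Section 2.10 | Section 2.15 |
|---|---|---|
| In the efficacy analysis? | No | Yes under ITT: randomised, with at least one assessment |
| If the patient counts as a dropout or termination? | Removed | Kept, last value carried forward |
| Exclusion limited to the per-protocol set? | Not stated | Not stated |

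The term section 2.10 uses for such a patient most naturally means dropped out. That is an inference, but on that reading the two sections conflict a second time, since section 2.15 retains dropouts.

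**Step 2. The rules can give different results for the same patient.** Section 2.12.2 calls treatment effective if CSBM per week rises by at least 1. If only the baseline value is available, carrying it forward gives a change of 0. Section 2.15 would then count the patient as not effective, while section 2.10 removes the patient from numerator and denominator. A patient with day-14 or day-28 data could fall on either side of the threshold.

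**Step 3. Size.** The article gives no expected rate of serious events or of unblinding, no power calculation and no expected response, so there is no planned figure to reproduce. The arm size is consistent: 4 x 23 = 92 per subtype. What follows is an illustration only.

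Inputs: n = 23 per arm (section 2.6); r = 12 responders (assumed); k = patients excluded from that arm (assumed 1 to 3).

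- Share of the arm removed = k/23.
- Rate if all k are non-responders = 12/(23 - k).
- Rate if all k are responders = (12 - k)/(23 - k).
- Rate with no exclusion = 12/23 = 52.2%.

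| k | Share removed | All non-responders | All responders |
|---|---|---|---|
| 1 | 4.3% | 12/22 = 54.5% (+2.4) | 11/22 = 50.0% (-2.2) |
| 2 | 8.7% | 12/21 = 57.1% (+5.0) | 10/21 = 47.6% (-4.6) |
| 3 | 13.0% | 12/20 = 60.0% (+7.8) | 9/20 = 45.0% (-7.2) |

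Changes are in percentage points, taken from unrounded rates. With two exclusions, one responder and one non-responder, the rate is 11/21 = 52.4%, a change of +0.2. The sign depends entirely on the outcomes of the patients removed.

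**The case against.** **The exclusion could be meant for the per-protocol set only.** Section 2.15 invokes both principles, and a per-protocol exclusion would be compatible with it. That is a fair guess at the intention, but section 2.10 names efficacy without restriction, so the text as written still conflicts with ITT. The exit criteria in Table 1 are not shown, and any handling rule there cannot be checked.

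**The effect may be negligible.** The trial calls itself exploratory, treatment lasts 28 days, and a patient is lost only if an event occurs and the letter is then opened. This stands. It limits the severity but does not remove the contradiction.

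**The illustration uses the responder rule, whereas section 2.15 assigns a rank test to CSBM per week.** This also stands. The figures show how far a few exclusions can move an arm of 23, not the effect on the planned test.

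A reader might infer two stronger claims that the documents do not support:

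- **That the patients removed are always those harmed by treatment.** Section 2.13 defines adverse events as caused by treatment, but the trigger in section 2.10 also covers emergencies, which need not be. Nor does every serious event lead to an opened letter.
- **That the exclusion flatters the arm with more harm.** That needs the excluded patients to be mainly poor responders, which the article nowhere says. If they were responders, the arm would look worse.

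**Conclusion.** The point holds as a contradiction between two stated rules on who is in the efficacy analysis. It is not a detail left to a fuller document: the article states both rules, and a later plan would have to overrule one of them. Followed literally, section 2.10 breaks the ITT comparison through a post-randomisation exclusion that may differ by arm and can bias the result either way.

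The size is unknown and may be zero. Each exclusion removes 4.3% of an arm of 23. In the two-patient example the response rate moves by +5.0 or -4.6 points at the extremes, resting on the assumed 12 responders and two exclusions. Severity is moderate: the sections should be reconciled before any letter is opened, but nothing in the documents shows that the trial's conclusions would change.

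**What to change.** In section 2.10, replace the general exclusion from efficacy with a rule of this kind: a patient whose emergency letter is opened stays in the ITT efficacy analysis in the randomised arm; all data collected are used, including the already scheduled day-28 assessment where the patient agrees; remaining gaps are handled by the plan's missing-data method; and exclusion applies to the per-protocol analysis only. A short cross-reference in section 2.15 would keep the two sections aligned.

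The wording change is a sentence or two. The one practical cost is completing scheduled assessments for the few patients concerned, who might otherwise have left the study. The sample size does not change, and neither do treatment, the decision to open a letter or the safety analysis.

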### Quality control

2.11

Participants’ DQ will be assessed at the baseline and after the intervention. The foods involved are in LVD content.

### Data collection

2.12

#### Baseline information

2.12.1

Baseline information will include demographic data and clinical data from the participants after allocation. Demographic data includes gender, age, height, weight, nationality, occupation, and education level. Clinical data includes past medical history, drug allergy history, the history of medications used to treat or induce constipation, dietary habits in the past year (see Supplementary Table 3),^[21]^ the primary outcome and secondary outcomes.

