### Interventions

2.8

After the patients are enrolled, they will finish a questionnaire (baseline information) and the relevant examinations (48-h GITT, HRAM, FFD, BR, LKF). Previous studies have reported Forlax and Chinese herb as effective drugs for the treatment of TFC^[9]^ and aTFC^[20]^ respectively. So, the drug used for the treatment of TFC subtype is Forlax. The placebo will be a kind of white powder made from orange essence, saccharin sodium and dextrin (Shanghai Aipu Food Industry Corporation) according to 0.2:0.015:100 (w/w) and is similar to Forlax in shape and color. Both Forlax and placebo will be vacuum packaged as 10 g per pack using same type of aluminum foil. The drug in aTFC subtype will be Chinese herb powder dried by Chinese herb decoction (Tongrentang Chinese Medicine) from clinical prescription (see Table 2), and the placebo will be a kind of brown powder made from caramel pigment and dextrin (Shanghai Aipu Food Industry Corporation) at 0.4:10 (w/w). Both the Chinese herb powder and placebo will be vacuum packaged as 15 g per pack using same type of aluminum foil. The drugs and placebos will be taken twice a day, one pack at a time, flushed with warm boiled water, half an hour after breakfast and dinner. The contents of LVD are as following:

(1)Taboo spicy (especially chili, pepper), irritating food, wine, fried food, grilled food, dry nuts, mutton, leek, toonasinensis and so on.(2)Avoid meat, eggs, milk, drinking coffee and strong tea.(3)The staple food are cereals and grains, take vegetables and fruits as much as possible.(4)Eat medicinal gruel: millet (main ingredients), coix seed, red bean that are mixed and cooked and eaten 1 to 2 times a day.(5)More than half of the staple food is potato (such as sweet potato and potato).(6)Diet must accord with three meals a day, regular quantitative with abstinence from drinking

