**Table 2 T2:**
[figure not shown]
The component of Chinese herb powder.

Patients with diet intervention should follow the above items and patients without diet intervention will continue their previous eating habits. The treatment period will last for 28 days. During the treatment period, patients will be required to keep a diary about diet and defecation. The diet diary will be designed with a semi-quantitative food frequency method, and the defecation diary will gather information about sensation, stool shape and duration of each defecation. On the 14th day, patients will be followed up via telephone to find out the situation during the treatment and count the average times of CSBM per week, the average scores of constipation symptoms and TCM syndrome in the first 14 days. After 28 days of treatment, a second follow-up will be carried out to understand situation of constipation (the same to the first follow-up) and to ask the patients to finish the examinations (48-hour GITT, HRAM, BR, LKF). Fecal flora of fresh stool (<30 minutes) from patients will also be reviewed and the diaries will be taken back. During the intervention, the patients will keep in touch with the researchers for queries about the treatment if any to control the exit rate and any other drugs that can relieve constipation are forbidden.

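### Baseline outcomes are recorded after allocation, so knowledge of the diet arm can influence them, and sections 2.2 and 2.9 disagree on what the assessors are blinded to

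*Protocol article*

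**What the plan says.** **Timing.** Section 2.12.1: "Baseline information will include demographic data and clinical data from the participants after allocation". The clinical data listed there end with "the primary outcome and secondary outcomes". Section 2.8 puts the baseline work-up after enrolment: "After the patients are enrolled, they will finish a questionnaire (baseline information) and the relevant examinations". Section 2.9 puts the handover of the allocation at the same stage: "When a patient is enrolled, an envelope with a sequence number on its surface will be passed to the researchers".

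**Knowledge of the arm.** Section 2.9: "The researchers and patients will know whether diet is interfered and the drug number only, but not the corresponding drug or placebo group". It adds that blinding is confined to the drugs because the diet is hard to mask. Section 2.2 also says participants learn through their enrolment number whether they are on the diet.

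**Assessment.** Section 2.2 has outcomes at baseline, day 14 and day 28 evaluated "by researchers blinded to the groups". The four groups in 2.9 are diet + drug, diet + placebo, drug, and placebo.

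**Use of baseline.** Section 2.12.2 counts treatment as effective when CSBM per week rises by 1 or more from before to after the intervention. Section 2.12.3 grades the constipation symptom scale (CSS) and the TCM syndrome scale (TCMSS) by percentage improvement or reduction. Section 2.15 applies a rank test to CSBM per week, fills missing values by LOCF, and analyses randomised patients who have at least one assessment, with the baseline one counting.

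**The concern.** A baseline protects a randomised comparison because allocation cannot have affected it. Taken after allocation, from people who may already know whether they are on the diet, it loses that protection. Whether an evacuation felt complete, how strong the discomfort was on a 0 to 10 scale, and whether a syndrome is mild or moderate are all matters of judgement. A shift in how these are reported at baseline would appear as a difference in improvement that the diet did not cause.

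The exposed comparisons are those the trial exists to make. Section 2.1 aims at the effect of the diet and its supplementary effect to drugs.

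The blinding statement adds to this. A reader of 2.2 alone would take the diet comparison to be assessor-blinded. Section 2.9 gives no support for that.

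**Working it through.** The plan states no figure on this point, so the check is a cross-reading, followed by an illustration on assumed values.

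**1. Order of events.** Sections 2.8 and 2.9 both place their steps at enrolment and do not order them against each other. Section 2.12.1 does: baseline data, outcomes included, follow allocation. The other two sections are compatible with that order, and nothing in the text reverses it.

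**2. What is known by then.** Under 2.9, researchers and patients know the diet assignment and a drug number, but not drug or placebo. So the diet contrasts (A versus C, B versus D) are exposed. The drug contrasts within a diet condition (A versus B, C versus D) are not.

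**3. Where baseline enters the analysis.**
- The response rule in 2.12.2 is after minus before, so baseline enters directly.
- CSS and TCMSS percent improvement need a starting value, so baseline enters directly.
- The rank test in 2.15 is on CSBM per week, and the sentence does not say whether that is a change or a post-treatment value. If it is post-treatment, baseline enters only where LOCF carries a baseline forward as the final value. An under-reported baseline in a diet arm would then count against the diet, the opposite of its effect on the response rule.
- A patient who learns the arm and leaves before the baseline assessment has no assessment, and so falls outside the 2.15 analysis set for a reason that may depend on the arm.

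**4. Blinding.** The groups are defined by diet as well as drug. Blinding to the groups therefore implies blinding to diet, which 2.9 denies for the researchers. No separate diet-blind assessor is described.

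**5. Illustration only.** The documents give no SD and no estimate of reporting shift. Assume no true diet effect, 23 patients per arm (2.6; 4 × 23 = 92 per subtype), two-sided 0.05, a normal approximation in place of the rank test, a test on change, an SD of change of 1.0 to 2.0, and baseline under-reported by b CSBM per week in one diet arm.

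SE = SD × √(2/23). False-positive rate = Φ(b/SE − 1.96) + Φ(−b/SE − 1.96).

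For SD 1.5 and b = 0.5: SE = 1.5 × 0.295 = 0.442, b/SE = 1.13, rate = Φ(−0.83) + Φ(−3.09) = 0.204.

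| Assumed b | SD 1.0 | SD 1.5 | SD 2.0 |
|---|---|---|---|
| 0 | 0.050 | 0.050 | 0.050 |
| 0.25 | 0.136 | 0.087 | 0.071 |
| 0.5 | 0.396 | 0.204 | 0.136 |

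For the response rule, assume also a mean change of 0.5. The proportion responding is 1 − Φ((1 − 0.5 − b)/SD). With b = 0 it is 0.309, 0.369 and 0.401 for the three SDs; with b = 0.5 it is 0.500 for each.

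These numbers show how sensitive arms of 23 would be to a shift. They do not show that a shift would occur.

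**The case against.** **The order rests on one phrase.** Section 2.9 says when the envelope reaches the researchers, not when it is opened or when the patient is told. Figures 1 and 2 are not shown and may give a safer order. This stands as a caution: disclosure before baseline is permitted by the text, not proved. But 2.12.1 as written would still need correcting.

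**Partial blinding is disclosed.** The heading of 2.9 says so, 2.2 itself goes on to say that drug versus placebo is what is concealed, and the Discussion lists the difficulty of blinding the diet as a limitation. The sentence in 2.2 may be loose wording, or the researchers there may be different people from those in 2.9. A reader might infer that no diet-blind assessment takes place at all; the text does not establish that. It establishes two statements that cannot both stand as worded. The stated limitation mentions neither the baseline timing nor this conflict.

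**Stronger readings that the document does not support.** A reader might infer that the primary test is necessarily biased through its baseline; 2.15 does not say that the test uses change. A reader might add that baseline is spoiled as a covariate; no covariate-adjusted model is stated. A reader might also see a mismatch of instruments, since 2.8 says "During the treatment period, patients will be required to keep a diary about diet and defecation" while baseline is a questionnaire. That would apply to all arms alike, and the article does not say how the diary feeds the weekly count.

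**The trial is exploratory.** True, but the Discussion expects reliable evidence of dietary efficacy from it, and the label does not make a post-allocation baseline harmless.

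**Conclusion.** The point holds in a limited form. As written, baseline CSBM, CSS and TCMSS are collected after allocation in a trial where patients and researchers know the diet assignment. This leaves the 1-per-week response and the percent-improvement outcomes open to avoidable bias in the two diet contrasts. Drug versus placebo within a diet condition is not affected. The rank test on CSBM is affected if it uses change; if it uses post-treatment values, it is affected only through baseline values carried forward.

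The size and direction of any bias cannot be derived from the document, and the figures above are conditional on assumed shifts and SDs. The conclusion about timing does not depend on them. The conflict between 2.2 and 2.9 is a separate defect of the text.

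The fix removes only the baseline part. Patients who know their diet will still report their own outcomes during treatment, and that is inherent in the design.

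**What to change.** 1. Change 2.12.1 so that all baseline outcome data are completed and locked before the allocation envelope is released, and align 2.8 and 2.9 with that order. This also closes the gap in the 2.15 analysis set, because every randomised patient will then have a baseline assessment.
2. Reconcile 2.2 with 2.9. Either state that blinding covers drug versus placebo only, or have existing staff who do not see the diet arm read the transit (GITT) and manometry (HRAM) results, and say which outcomes this covers.
3. Optional: a defecation diary before randomisation. It would give a baseline recorded in the same way as the later values, but it delays treatment and is not needed to cure the timing problem.

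Items 1 and 2 cost a reordering of visit steps and some wording. The envelope would have to wait for the 48-hour transit test, which 2.8 already lists in the work-up on enrolment. Item 1 has to be in place before patients are enrolled, because a baseline taken after disclosure cannot be repaired in the analysis.
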